## Abstract

**Background:**

Chronic neck pain is a common condition in the adult population. More research is needed to evaluate interventions aiming to facilitate beneficial long-term change. We propose to evaluate the effect of Alexander Technique lessons and acupuncture in a rigorously conducted pragmatic trial with an embedded qualitative study.

**Methods/Design:**

We will recruit 500 patients who have been diagnosed with neck pain in primary care, who have continued to experience neck pain for at least three months with 28% minimum cut-off score on the Northwick Park Neck Pain Questionnaire (NPQ). We will exclude patients with serious underlying pathology, prior cervical spine surgery, history of psychosis, rheumatoid arthritis, ankylosing spondylitis, osteoporosis, haemophilia, cancer, HIV or hepatitis, or with alcohol or drug dependency currently or in the last 12 months, or actively pursuing compensation or with pending litigation.

The York Trials Unit will randomly allocate participants using a secure computer-based system. We will use block randomisation with allocation to each intervention arm being unambiguously concealed from anyone who might subvert the randomisation process.

Participants will be randomised in equal proportions to Alexander Technique lessons, acupuncture or usual care alone. Twenty 30-minute Alexander Technique lessons will be provided by teachers registered with the Society of Teachers of the Alexander Technique and twelve 50-minute sessions of acupuncture will be provided by acupuncturists registered with the British Acupuncture Council. All participants will continue to receive usual GP care.

The primary outcome will be the NPQ at 12 months, with the secondary time point at 6 months, and an area-under-curve analysis will include 3, 6 and 12 month time-points. Adverse events will be documented. Potential intervention effect modifiers and mediators to be explored include: self-efficacy, stress management, and the incorporation of practitioner advice about self-care and lifestyle. Qualitative material will be used to address issues of safety, acceptability and factors that impact on longer term outcomes.

**Discussion:**

This study will provide robust evidence on whether there are significant clinical benefits to patients, economic benefits demonstrating value for money, and sufficient levels of acceptability and safety.

**Trial registration:**

Current Controlled Trials ISRCTN15186354

## Background

### The problem to be addressed

Optimal care for uncomplicated chronic neck pain has yet to be established [1] Despite decades of research, little advance has been made in reducing the health and economic burden of chronic neck pain [2]. There is some evidence that exercise, mobilisation and manipulation are beneficial [1], although there are concerns regarding the safety of neck manipulation. While psycho-social factors are associated with increasing chronicity, [3] and improved coping strategies result in better outcomes [4], interventions that facilitate change in illness-related behaviours and habits are needed [2]. Many people with chronic neck pain consult acupuncturists and Alexander Technique teachers, largely outside the NHS, and while these interventions are considered relatively safe, the evidence on health outcomes is as yet inconclusive [1].

### The principal research questions to be addressed

Our principal research question asks: What is the clinical and economic impact when comparing acupuncture treatment plus usual care to usual care alone, and Alexander Technique lessons plus usual care to usual care alone in patients with chronic neck pain who are recruited from primary care? We will also compare acupuncture to Alexander Technique lessons to estimate possible clinical differences. We will determine whether putative benefits are clinically worthwhile. We will compare the cost-effectiveness of the alternative strategies, and if these interventions are at an additional cost to usual care, then we will ascertain whether they are worth paying for in terms of cost per Quality Adjusted Life Year (QALY) gained, in the context of the National Institute for Health and Care Excellence (NICE) threshold, which ranges from £20,000 to £30,000 [5]. We will also assess the acceptability and safety profile of acupuncture and Alexander Technique lessons for this patient group. In this study, we have used our pilot trial on acupuncture for chronic neck pain (ISRCTN06223266) [6] to inform the design of the full-scale trial.

### How the results of the trial will be used to change patient management

Acupuncture and Alexander Technique lessons are two interventions that are not widely provided within the NHS, yet have the potential to safely deliver longer term benefits for spine-related conditions. Both interventions involve individualised sessions that include support for sustained improvement in health, based on changes in self-care and/or lifestyle [7,8]. Using pragmatic trial designs, where the trial practitioners can provide interventions similar to what they normally would provide in their routine care, long-term benefits have been observed in acupuncture at 12 and 24 months for headache and back pain respectively [9,10]. Acupuncture was found to be cost-effective [11,12]. A Medical Research Council funded trial of Alexander Technique lessons for back pain patients found long-term clinical and cost-effectiveness benefits at 12 months [13,14].

NICE now recommends acupuncture as a referral option within primary care for people with persistent low back pain [15]. The clinical effectiveness and cost-effectiveness illustrated by our York-based trial [11] was central to that decision. The proposed trial has a similar design, and therefore the results will help to inform decision making by policy makers, providers and commissioners as well as patients. If it is found that either of these two interventions is not effective, then decisions to limit the use of these interventions within the NHS will also be in the interests of both the NHS and patients.

### How the proposed trial will differ from recently completed trials elsewhere in the United Kingdom or internationally

The proposed trial will complement the two UK-based low back pain trials discussed above, one of acupuncture and one of Alexander Technique lessons [9,13]. A trial conducted in Germany found that acupuncture delivered by physicians in conjunction with routine care was clinically beneficial for chronic neck pain when compared to routine care alone at the end of treatment (that is, 3 months) [16], and also demonstrated cost effectiveness with cost per QALY gained being estimated at €12,469 at 3 months [17]. The proposed trial on chronic neck pain adds an Alexander Technique lesson arm, extends the period of measurement to 12 months, and focuses on a UK-based primary care population. In addition to assessing changes to physical parameters and quality of life, another difference will be our focus on the ways the interventions impact on thoughts/beliefs, self-perceptions, self-efficacy and empowerment, and the potential for these to enhance outcomes over the longer term [7,8].

## Methods/Design

### Details of the trial

The study is a three-arm pragmatic randomised, controlled trial to evaluate the effectiveness, cost effectiveness, safety and acceptability of acupuncture and Alexander Technique lessons for patients with chronic neck pain. The three arms are: acupuncture plus usual care, Alexander Technique lessons plus usual care, and usual care alone. Participants will be recruited from primary care and randomised to one of the three arms after we have obtained their informed consent to participate in the trial and their completed baseline questionnaire and after they have been screened for eligibility.

This pragmatic design will best answer practical questions regarding the clinical and economic implications of offering these healthcare options in primary care within the context of existing provision. Our proposal builds on two previous pragmatic trials of acupuncture and Alexander Technique lessons for back pain patients [9,13], both of which were designed to support individualised patient-practitioner interactions and active patient involvement in strategies for longer term change [7,8]. Because both interventions involve active learning (both theoretical and practical/experiential) by the participant, identifying an appropriate and adequate sham is problematic. It is accepted that in addition to the active learning components there are components associated with nonspecific effects (for example, empathy). Yet, even if it were possible to separate out these nonspecific components, there may be an unknown loss of synergy between interacting components [18]. Additionally, in principle, it is difficult to provide scientifically robust sham treatments as controls because the specific mechanisms and causal pathways of acupuncture and Alexander Technique lessons are not known. For example it is unknown whether there are neural pathways associated with both specific and nonspecific effects, such as those associated with self-healing. One resolution to these difficulties is to bypass the question regarding the relative impact of specific and nonspecific components, and to address a different research question, namely asking, ‘What is the overall benefit?’ For a pragmatic trial to be ‘positive’, the results must, as a minimum, meet four quantitative challenges: statistical significance, clinical relevance, adequate safety and worthwhile cost-effectiveness. To summarise, the pragmatic design offers best value by providing data that are immediately applicable to patients and providers with real-world comparisons that will assist policy and decision-makers.

We will collect additional data in order to explore:

1) the impact of potential effect modifiers, including preference, belief and expectation, factors often associated with ‘placebo’ or nonspecific effects

2) the impact of potential effect mediators, including self-efficacy, stress management, and changes in self-care and/or lifestyle, and their association with longer-term outcomes

3) the variation in patient outcome between individual practitioners

4) the identification of sub-groups of patients that respond better/worse to the interventions.

### Details of trial interventions

Twenty 30-minute Alexander Technique lessons (600 minutes in total) will be provided by teachers registered with the Society of Teachers of the Alexander Technique (STAT) with at least three years of teaching experience and evidence of a commitment to their continuing professional development. The decision to provide 20 lessons was based on a.) the experience of the ATEAM trial [13], which offered either 6 or 24 lessons and b.) from our consultation with Alexander Technique teachers. Twenty lessons were considered sufficient to consolidate the learning necessary for sustainable change to take place. The 30-minute lesson time was derived from the overall contact time of 600 minutes, equivalent to the acupuncture intervention. The first lesson will be 15 minutes longer to allow the participant to explain his/her problem and to answer questions, and also to allow the teacher to explain what the Alexander Technique is and what will be involved. Subsequent lessons will each contain 30 minutes of active teaching time with the content based on a protocol that was used in the recent ATEAM back pain trial [13] and on further consultation with STAT. Generally lessons will be weekly, with the option of being twice-weekly initially and fortnightly towards the end of the series, and are expected to be completed within five months. The scheduling of appointments will be based on normal practice, involving both the teacher’s discretion and the participant’s preference. Alexander Technique lessons provide an individualised approach to developing lifelong skills for self-care that help people recognise, understand, and avoid poor habits adversely affecting postural tone and neuromuscular coordination [19]. Lessons incorporate specific principle-driven patient-practitioner interactions designed to empower patients and engage them as active partners in their own recovery [8]. All participating teachers will use both verbal and hands-on instruction in line with the National Occupational Standards Skills for Health guidelines. Teachers will participate in a one-day induction workshop orientated towards the research process and will document components of lessons and adherence in logbooks.

Twelve 50-minute sessions of acupuncture (600 minutes in total) will be provided by professional acupuncturists who practise a style of acupuncture that is based on traditional Chinese medicine (TCM). The decision to provide 12 sessions was based on providing equivalence to the 600 minutes provided by Alexander Technique teachers, given that typically a session lasts 50 minutes. Acupuncturists will be registered with the British Acupuncture Council with at least three years of experience and provide evidence of a commitment to their continuing professional development. The first session will be 15 minutes longer to allow the patient to explain his/her problem and to answer questions. The scheduling of appointments will be based on normal practice, which will involve both the practitioner’s discretion and the participant’s preference. All sessions are likely to be completed within five months. Acupuncture involves the insertion of fine needles at points indicated by the diagnosis combined with customised explanations and lifestyle advice that is specific to the acupuncture diagnosis. In this way, acupuncture treatments are provided so as to optimise potential longer term benefits. To support this process, we will use a previously tested acupuncture treatment protocol [6] that incorporates specific theory-driven patient-practitioner interactions designed to engage patients as active partners in their own recovery [7]. All practitioners will participate in a one-day induction workshop (see above). Practitioners will document components of treatment and adherence in logbooks.

Procedures used to identify, shortlist, and recruit Alexander Technique teachers and acupuncturists will be based on those procedures successfully employed in the ACUDep trial, which compared acupuncture, counselling and usual GP care for the treatment of depression (ISRCTN63787732) [20]. As a starting point we shall seek to identify geographical clusters of suitably qualified and experienced Alexander teachers and acupuncturists, who together would be capable of delivering both interventions to trial participants living in Northern England. Each geographical cluster should consist of no less than two Alexander teachers and two acupuncturists, ideally within a two-mile radius. However, additional consideration will be given to local issues relating to public transport and accessibility. Given that patients will be recruited from nearby general practices, most participants will live within walking distance of both an Alexander teacher and acupuncturist. This should serve to minimise any burden on participants in terms of travel, maximise attendance rates, and help to maintain equipoise between both intervention groups. Alexander teachers and acupuncturists who are shortlisted by the research team, and are willing to support the trial, will then be required to submit a curriculum vitae for review, together with any evidence for recent continuing professional development activities. This review process will be conducted in conjunction with relevant professional members of the trial management group. Alexander teachers and acupuncturists who are finally selected will need to provide evidence of professional indemnity insurance and undergo Criminal Records Bureau clearance.

All participants will remain under the care of their GP and will receive usual NHS treatments as well as other care throughout the trial. This is expected to include GP consultations, typically involving brief advice lasting perhaps 10 minutes per consultation plus the offer of prescribed painkillers. Some participants will also be taking over-the-counter medication and/or consult with NHS and non-NHS practitioners. We will record and measure the full range of what constitutes usual care that all participants continue to receive throughout the trial period. This will include additional acupuncture and Alexander Technique lessons, whether paid for out-of-pocket or provided free within the NHS.

### Methods for protecting against other sources of bias

Blinding to intervention is not relevant for the proposed trial, which is designed to answer the pragmatic research question that relates to the overall benefit to patients. To estimate the potential impact of the nonspecific components of preference, expectation and belief, we will measure these at baseline and evaluate their impact on outcome, as we have done in previous trials for preference [21] and belief [9]. The York Trials Unit will randomly allocate participants using a secure system ensuring that allocation is unambiguously concealed from anyone who might subvert the randomisation process. We will use block randomisation, which will give us as balanced an allocation as possible within each cluster of participants from each GP practice. Postal questionnaires will be used to collect outcome data after randomisation to ensure no clinician or researcher who knows the allocation can influence the process of data recording, collection and analysis. Intention-to-treat analysis will be used to ensure that the groups will be compared as randomised. Care will be taken to map the components of each intervention in all three arms of the trial, so that we can adequately describe inputs associated with putative differences between group outcomes. Bias due to attrition will be minimised by carefully following up all the participants including drop outs. In order to reduce attrition rates, the final follow-up questionnaire will be accompanied by a £5 incentive to complete it.

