### Proposed sample size and a description of the power calculations

We will recruit 500 participants in total to the trial. Our sample size calculations were performed for a simple comparison of two groups. From our pilot, the standard deviation of the primary endpoint, the Northwick Park Questionnaire (NPQ), was 16%, and the correlation between baseline and 3-month NPQ was 0.69 [6]. A clinically meaningful difference on the NPQ is 5 percentage points [43], a 0.31 effect size. With 90% power and alpha = 5% we would require 113 participants per arm after adjusting for baseline. We are aiming for a loss to follow-up of 20% but in our estimate of sample size we are conservative, allowing for 30% loss to follow-up. Randomising into three equally sized groups, our required total sample size will be 500.

For our primary comparison, we will estimate the difference in mean score from the NPQ at 12 months between the acupuncture and control groups and between the Alexander Technique lessons and control groups, after adjustment for baseline pain score using analysis of covariance. Each of our two active interventions tested against control can be interpreted quite independently of the other. This does not constitute a problem of multiple testing, as there might be if we had two different kinds of acupuncture. If we find acupuncture to be significantly better than the control, then we would conclude that it worked. But this test would tell us nothing about Alexander Technique lessons versus control. Therefore when testing two independent hypotheses, we do not need to use multiple comparison procedures. We will, as a secondary analysis, estimate the clinical difference between acupuncture and Alexander Technique lessons.

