### A summary of the statistical analysis plan

Analysis will be by intention-to-treat. All of those randomly allocated will remain in their group for analytical purposes irrespective of whether or not they actually take up or fully adhere with the intervention. Statistically we will use analysis of covariance to control for baseline values. Multiple imputation will be used to account for missing values.

As this is a pragmatic trial, participants are offered, but may not receive a full course of sessions or lessons. Some may discontinue if they get better before the end of their course. Others may discontinue if they perceive no benefit. In a trial of Alexander Technique lessons for low back pain patients, average attendance was either 5 out of 6 offered lessons, or 20 out of 24 lessons offered [13]. We will incorporate Complier Average Causal Effect (CACE) analysis to control for any dilution effects of people not taking up their allocated intervention [45]. We will also ascertain whether there is a relationship between levels of attendance and outcome, and whether outcomes are better or not for those participants who have attended at least 75% of sessions.

To evaluate trajectories of change from the text message scores, we will fit a common curve for each group using polynomial regression. We will use a polynomial within-subject, by analysis of covariance, to enable us to plot an empirical curve for each group. We can compare the three groups statistically to test for interactions between intervention group and time. Moreover these text scores will provide useful data for multiple imputation for missing data.

We will use regression models to explore whether preference, belief or expectation are treatment effect modifiers. We will explore whether potential treatment effect mediators (self-efficacy, stress management, incorporation of advice about self-care and lifestyle) might be associated with longer term change.

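### Allocation is balanced within GP practice, but the stated primary ANCOVA names only the baseline score; practice should enter as a random intercept (minor)

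*Protocol article*

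**What the plan says.** Three places in the protocol article bear on the point.

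- **Methods for protecting against other sources of bias** describes the allocation: "We will use block randomisation, which will give us as balanced an allocation as possible within each cluster of participants from each GP practice". The word stratified is not used, but balance inside each practice implies blocks formed by practice.
- **Proposed sample size and a description of the power calculations** sets out the primary comparison: each active arm against usual care on 12-month NPQ, "after adjustment for baseline pain score using analysis of covariance". It names the outcome, time point, contrasts and covariate, and gives the position on multiplicity.
- **A summary of the statistical analysis plan** repeats the method: "Statistically we will use analysis of covariance to control for baseline values".

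Neither analysis section names practice. Differences between practitioners are assigned to a separate analysis. The recruitment section expects about 15 participants from each of 33 practices, and the Discussion places the trial in York, Leeds, Sheffield and Manchester.

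**The concern.** A factor used to balance the allocation should normally appear in the analysis. Balance on practice means that between-practice differences largely cancel from the difference between arm means, so the true variance of that difference is smaller. An ANCOVA without practice does not see the cancellation. It counts the between-practice variation as residual noise and, from this source, reports a standard error that is too large.

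The consequence is a slightly conservative test and slightly wide intervals in both primary comparisons and in the secondary comparison of the two active arms. With practices spread over four cities, some between-practice variation in NPQ is plausible.

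**Working it through.** **Inputs from the article (sample size section).** The SD and baseline correlation: "was 16%, and the correlation between baseline and 3-month NPQ was 0.69". The target difference: "A clinically meaningful difference on the NPQ is 5 percentage points [43], a 0.31 effect size". The requirement: "With 90% power and alpha = 5% we would require 113 participants per arm after adjusting for baseline". The attrition allowance is 30%, with three equal arms and a total of 500.

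**Input assumed.** The residual practice ICC, after baseline adjustment, is not given. It is written ρ and taken as 0.02, 0.05 and 0.10.

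**Step 1: reproduce the plan's figure.**
- Baseline-adjusted SD = 16 × √(1 − 0.69²) = 11.58.
- n per arm = 2 × (1.960 + 1.282)² × 11.58² / 5² = 112.7, rounded up to 113. This matches.
- After 30% loss: 113 / 0.7 = 161.4, rounded up to 162 per arm; 3 × 162 = 486, within 3% of the stated 500.

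No term for practice enters this calculation. The planned 90% power takes no credit for balance on practice.

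**Step 2: effect of omitting practice under exact balance.** With 113 per arm:
- Reported SE = 11.58 × √(2/113) = 1.541.
- True SE = 1.541 × √(1 − ρ), so the reported SE is too large by a factor 1/√(1 − ρ).
- Actual type I error = 2 × [1 − Φ(1.96/√(1 − ρ))].
- Power without practice = Φ[(5 − 1.96 × 1.541)/true SE].
- Power with practice = Φ[5/true SE − 1.96].

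| Assumed ρ | True SE | SE too large by | Type I error | Power without practice | Power with practice |
|---|---|---|---|---|---|
| 0.02 | 1.525 | 1.0% | 4.8% | 90.3% | 90.6% |
| 0.05 | 1.502 | 2.6% | 4.4% | 90.6% | 91.5% |
| 0.10 | 1.462 | 5.4% | 3.9% | 91.2% | 92.8% |

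**Step 3: allow for loss, and compare two ways of fitting practice.** Exact balance is an idealisation, so the design was simulated: 33 practices, 5 participants per arm in each, 30% random loss and 4,000 runs per setting.

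Practice as a random intercept (REML, three arms):

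| ρ | Power without / with | Type I error without / with | Reported SE, without relative to with |
|---|---|---|---|
| 0 | 90.1% / 90.3% | 5.3% / 5.4% | +0.4% |
| 0.02 | 90.4% / 90.7% | 4.9% / 5.2% | +0.9% |
| 0.05 | 90.5% / 91.2% | 4.7% / 5.3% | +2.1% |
| 0.10 | 91.0% / 92.5% | 4.3% / 5.2% | +4.5% |

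The Monte Carlo error on type I error is about 0.35 points.

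Practice as fixed effects (two arms compared), power without / with: 90.2% / 89.2% at ρ = 0; 90.6% / 90.1% at 0.02; 90.9% / 90.5% at 0.05; 90.9% / 91.3% at 0.10. Fixed effects show no gain up to about 0.05, because they use up degrees of freedom and strata that become unbalanced after loss give less information. The random intercept did not lower power at any setting.

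**The case against.** **Silence is not exclusion.** The analysis section is headed "A summary of the statistical analysis plan", the document is a condensed article, and the full plan is not shown and may include practice. No sentence says that practice is left out. This stands as a limit on the wording: the article names only the baseline score, and one cannot say that practice is excluded. It does not remove the point, because the article does state a specific primary model, and that model leaves out the factor by which it balances allocation.

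**Planned power is not at risk.** A reader might infer that the trial loses power it had already bought. The documents do not support that: the 113 per arm is reproduced without any credit for practice. A reader might also multiply the 500 by the ICC and call the result wasted participants. That ignores the 30% loss. It also treats an overstated standard error as lost information, although the balanced estimator already has the smaller true variance and only the test threshold is conservative.

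**The direction of the overall error is not settled.** A reader might conclude that the reported intervals will be conservative. Participants in the active arms are also clustered by acupuncturist or teacher, which the article leaves to a separate analysis. Ignoring that clustering makes the standard error too small. This objection stands: the conservative direction holds for the practice term alone.

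**Adjustment can cost power.** This is true of 33 fixed practice effects when the ICC is small. It does not carry over to a random intercept, as the simulation shows.

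**Balance is imperfect.** No block size is given, and incomplete blocks and attrition weaken the balance. This stands too, and it makes the overstatement somewhat smaller than the exact-balance formula gives.

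**Conclusion.** The mismatch between allocation and stated model is real but minor. For any positive residual practice ICC, omitting practice makes this component of the standard error too large. With the ICC assumed to be 0.02 to 0.10, the excess is about 1% to 5%, or 0.9% to 4.5% in the simulation with 30% loss. Type I error is about 4.8% to 3.9%. The power forgone is under 1 point up to 0.05 and about 1.6 points at 0.10.

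The treatment estimate is not biased by the omission, and false positives are not inflated by it. These sizes rest on an ICC that the article does not supply, on practice-level blocks that work as described, and on random loss. They do not include practitioner clustering.

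**What to change.** State that the primary 12-month NPQ model includes baseline NPQ and a random intercept for GP practice. Do not fit 33 fixed practice effects. Use the same practice term in the secondary outcome models and in the imputation model. If practice is to be omitted, give the reason.

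The cost is one model term on data already held, since the allocation itself used practice. No change to sample size, data collection or conduct is needed. The practitioner question is separate, and this term does not resolve it.
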